### Sample size

Based on our pilot study, we expect a reduction of 1.5 score points (sd 3.8) in the SDQ total difficulties score among the vulnerable sub group. To detect this effect with a statistical power of 80%, it requires a study sample of 102 pupils in each group; 204 in total.

To detect a reduction of 0.7 score points (sd 5.5) in the SDQ-total difficulties score among the total pupil population, requires a study sample of 971 pupils in each group; 1942 in total.

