### Recruitment

From May 2018—May 2019, we recruited schools through letters to school headmasters, local information meetings and by advertising on our website (www.mindfulness.au.dk) and other social media (Facebook and Instagram). We informed the school headmasters and interested teachers that the schools would be randomised to begin teacher training in 2019 (intervention group) or in 2020 (control group). We further informed that it was an obligation for each teacher to recruit one 5–8 class with 15 to 28 pupils in a year from randomisation corresponding to the time of the completion of teacher training in the intervention group to test the effectiveness of the “.b”-programme. We recruited schools in five blocks defined by the five regions. We have included a total of 110 Danish schools and 191 teachers who consented to participate in the trial; 27 schools and 56 teachers from the Capital Region of Denmark, 18 schools and 28 teachers from Region Zealand, 25 schools and 42 teachers from Region of Southern Denmark, 30 schools and 50 teachers from Central Denmark Region and 10 schools and 15 teachers from North Denmark Region.

We expect teachers to recruit approx. 2000 pupils in total for the trial. We expect that approx. 400 pupils will be in the vulnerable sub group resulting in a SDQ total difficulties score > 80% percentile at baseline.

In this real-life setting, it was not possible to include the pupils before the randomisation of the schools due to the logistics of teacher planning.

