The trial´s strengths include a well powered, rigorously effectiveness study design; a cluster RCT with 3 and 6-month follow-up data, including municipal and private schools across Denmark. The latter will enhance the external validity of the trial. The results of the trial will be of great relevance for decision-makers of mental health promotion and prevention programmes in adolescents in European countries. It is a strength that the “.b” teaching is embedded in the compulsory class room teaching making it possible to reach an entire population of school children without causing stigma to anyone. We use the same manualized “.b”-programme and school teacher training programme, currently being evaluated in a large scale trial in the UK [16]. An additional strength includes addressing implementation issues discovered in the UK [24] and adds support for implementation in our school teacher training programme. This added third part of our school teacher training programme is based on rigorous work of The Danish Association for Promoting Life Wisdom in Children”[30]. The first part of our school teacher training programme also differs to some extent from the teacher training route in the UK. The Danish school teachers participate in the evidence-based MBSR course, which is more intensive in both duration of sessions and home practice than the mindfulness programme used in the UK context [24]. MBSR is taught by MBSR teachers, who also take care of the the subsequent parts of the school teacher training programme. MBSR is delivered in groups consisting solely of school teachers in the project.

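### Both sample sizes are unclustered t-test figures, so the implied 80% power for the total pupil population (secondary aim) does not hold under school randomisation; the primary subgroup is adequately powered

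*Protocol article*

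**What the plan says.** The Sample size section of the protocol article has two calculations. For the primary population, "we expect a reduction of 1.5 score points (sd 3.8) in the SDQ total difficulties score among the vulnerable sub group", and "it requires a study sample of 102 pupils in each group; 204 in total"; the 80% power is written in this sentence. For the secondary aim, "To detect a reduction of 0.7 score points (sd 5.5) in the SDQ-total difficulties score among the total pupil population", the plan "requires a study sample of 971 pupils in each group; 1942 in total". No power is written in that second sentence, and neither calculation gives an alpha, ICC, cluster size or loss rate.

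Under Recruitment, 110 schools and 191 teachers have been included. "We expect teachers to recruit approx. 2000 pupils in total for the trial", and about 400 of these are expected in the vulnerable subgroup. The same section says that "it was an obligation for each teacher to recruit one 5–8 class with 15 to 28 pupils".

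Under Randomisation, schools are the units allocated. Under Statistical methods, the model has random effects for school, for teacher or class within school, and for pupil. The Discussion lists as a strength "a well powered, rigorously effectiveness study design", without limiting this to one of the two populations.

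**The concern.** The design and the analysis both recognise that pupils in one school or class resemble each other. The sample size does not. Positive correlation within schools makes 1942 pupils worth fewer than 1942 independent pupils, so a requirement computed for independent pupils is too small.

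For the vulnerable subgroup this hardly matters, because nearly twice the stated number is expected. For the total population the expected number barely exceeds the stated one. If that power is taken at face value, a null total-population result could be read as evidence that no effect of 0.7 points exists, although the trial may have had a much lower chance of finding one. The total population carries the argument for a population-based strategy that the Discussion addresses to decision-makers.

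**Working it through.** **Inputs from the protocol article.** Differences and SDs: 1.5 (3.8) and 0.7 (5.5). Stated sizes: 102 and 971 per group. Expected pupils: about 400 and about 2000. Schools: 110. Teachers, each with one class: 191.

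**Assumed, because not stated.** Two-sided alpha 5%; ICC 0.01 to 0.05 for the outcome as analysed; equal school sizes (unequal sizes would lower power somewhat); 5.5 as the SD of the analysed change; loss shown separately.

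**1. Reproducing the stated sizes.** The normal approximation n per group = 2 × (1.96 + 0.84)² × (SD/difference)² gives about 101 and 969. The exact t-test version gives 101.7 and 970.06, which round up to the stated 102 and 971. One-sided 5% would give 80 and 764; 90% power would give 135 and 1298. The match to the unit shows that the design effect used was 1 and the loss allowance zero. It also shows that 80% was used for the total population (power at 971 per group is 80%).

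**2. Margin for the total population.** 2000/1942 = 1.030. With m = 2000/110 = 18.2 pupils per school and design effect DE = 1 + (m − 1) × ICC, the margin is gone when ICC = 0.030/17.2 = 0.0017. If clustering acts at class level only (2000/191 = 10.5 per class), the limit is 0.030/9.5 = 0.003. Loss alone uses it up at 1 − 1942/2000 = 2.9%.

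**3. Power with clustering.** Power is computed at 1000/DE pupils per group. Pupils needed = 1942 × DE at the same 18.2 per school. Detectable difference = 2.80 × 5.5 × √(4 × DE/2000).

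| ICC | DE | Power for 0.7, 2000 pupils | Pupils needed for 80% | Detectable difference |
|---|---|---|---|---|
| 0 | 1.00 | 81% | 1942 | 0.69 |
| 0.01 | 1.17 | 75% | 2276 | 0.75 |
| 0.02 | 1.34 | 69% | 2610 | 0.80 |
| 0.03 | 1.52 | 64% | 2943 | 0.85 |
| 0.05 | 1.86 | 55% | 3610 | 0.94 |

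If 10% of the 2000 were lost, power would be 71%, 66%, 61% and 53% at ICC 0.01, 0.02, 0.03 and 0.05.

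**4. Primary subgroup.** 400/110 = 3.6 pupils per school, so DE is 1.03 to 1.13 over the same ICC range. Power for 1.5 points is about 97% to 96%, or about 94% to 92% with 20% loss. The 400 expected against 204 stated absorbs a combined inflation of 1.96.

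**5. The expected 2000.** 191 classes of 15 to 28 pupils give 191 × 15 = 2865 to 191 × 28 = 5348. The expected 2000 is 10.5 per teacher, below the smallest class allowed, and the article does not say why. With 2865 pupils in 110 schools and no loss, total-population power would be 86% at ICC 0.01, 79% at 0.02 and 62% at 0.05.

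**The case against.** Four points on the other side deserve weight.

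- **The primary aim is safe.** A reader might infer from the missing design effect that the primary analysis is underpowered. The article does not support that: about 400 pupils are expected, and the claim of good power holds for the primary question. Nor is type I error at issue, because the planned model includes school and class.

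- **The size of the shortfall is not established.** No ICC is given. The outcome is change from baseline, and school or class differences that are stable over time drop out of a change, so the relevant ICC is that of the change, which may be smaller than that of the score level. The article also does not say which SD 5.5 is. If it is the raw-score SD, the SD of change is 5.5 × √(2(1 − r)), with r the correlation between baseline and follow-up. At an assumed r of 0.7, power would be 92%, 89% and 77% at ICC 0.01, 0.02 and 0.05; at 0.6, about 84%, 78% and 65%; at 0.5 nothing is gained. This stands, and makes 75% to 55% one scenario. It does not rescue the calculation as printed, which uses 5.5 directly with independent pupils.

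- **Loss may be partly covered.** A reader might infer that no loss at all was foreseen. The 1942 contains none, but the 2000 lies so far below 191 full classes that it may already be net of teacher drop-out and parental opt-out. The article does not say. It would be equally unsupported to infer that only part of the 110 schools will contribute and to compute power on that footing.

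- **The 80% is not written for the total population.** It stands only in the subgroup sentence. It is implied for the other figure, and the reproduction confirms it.

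A fuller analysis plan might give an ICC, but it could not change the fact that the published 1942 contains none.

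**Conclusion.** The concern holds for the secondary aim. It is firm that both stated sizes omit clustering and loss, and that the total-population margin is only 3%, gone at an ICC of about 0.002 or loss of about 3%. The implied 80% is therefore not supported as written.

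The size is conditional. Power of about 75% to 55%, and a detectable difference of about 0.75 to 0.94 points instead of 0.7, rest on an assumed ICC of 0.01 to 0.05, 2000 analysed pupils spread over 110 schools, and 5.5 being the SD of the analysed change. This is an omitted design assumption; the arithmetic is correct for the formula used. The 102 per group shares the omission, without practical consequence for the primary analysis.

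**What to change.** Restate the Sample size section with:

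- alpha and sidedness, and the power used for each population;
- an ICC for the outcome as analysed, from the pilot or as a range, with the expected numbers of schools and classes;
- a loss rate, and whether the expected 2000 is before or after it;
- whether 5.5 is the SD of the change or of the raw score, with the baseline correlation if it is the latter;
- how about 2000 pupils follow from 191 teachers with one class of 15 to 28 each;
- the resulting power, or detectable difference, for the total population.

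In the Discussion, limit the statement on power to the primary vulnerable subgroup.

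The cost is a revised paragraph, one qualified sentence and probably a less favourable stated power for the secondary aim. No extra enrolment is asked for: the schools are already randomised and pupil data collection has begun.

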### Recruitment

From May 2018—May 2019, we recruited schools through letters to school headmasters, local information meetings and by advertising on our website (www.mindfulness.au.dk) and other social media (Facebook and Instagram). We informed the school headmasters and interested teachers that the schools would be randomised to begin teacher training in 2019 (intervention group) or in 2020 (control group). We further informed that it was an obligation for each teacher to recruit one 5–8 class with 15 to 28 pupils in a year from randomisation corresponding to the time of the completion of teacher training in the intervention group to test the effectiveness of the “.b”-programme. We recruited schools in five blocks defined by the five regions. We have included a total of 110 Danish schools and 191 teachers who consented to participate in the trial; 27 schools and 56 teachers from the Capital Region of Denmark, 18 schools and 28 teachers from Region Zealand, 25 schools and 42 teachers from Region of Southern Denmark, 30 schools and 50 teachers from Central Denmark Region and 10 schools and 15 teachers from North Denmark Region.

We expect teachers to recruit approx. 2000 pupils in total for the trial. We expect that approx. 400 pupils will be in the vulnerable sub group resulting in a SDQ total difficulties score > 80% percentile at baseline.

In this real-life setting, it was not possible to include the pupils before the randomisation of the schools due to the logistics of teacher planning.

### Randomisation

The schools were allocated into intervention or control schools in five runs, one for each region. Before allocation each school was given three characteristics: Type (municipal or private), size (1–499 or 500 + pupils) and number of teachers included in the project (1 or 2–3). For each region, the second author received a list of the schools with an anonymous id concealing the true identity of the schools. The schools were first selected randomly and then allocated to intervention or control attempting to balance the three characteristics between the two groups. Finally, this anonymous allocation list with the anonymous id was linked to the true identity of the school, creating the final allocation list.

The characteristics of the schools divided by randomisation group are shown in Table 2.

**Table 2 Tab2:** Characteristics of included schools in the SELFCARE project. A cluster randomised trial testing a school teacher training programme to deliver the “.b” programme in 110 schools covering schools in all five Danish regions

Characteristics	Intervention schools **n = 54**	Control schools **n = 56**
School type, municipal (%)	37 (69)	40 (71)
Total number of pupils, median (q1,q3)	430 (163,728)	490 (235,625)
Number of teachers included in the project (%)		
1 teacher	23 (43)	26 (46)
2 teachers	17 (31)	21 (38)
3 teachers	14 (26)	9 (16)
Number of teachers included in the project, in total	97	94

### Blinding

It was not possible to blind either intervention providers or study participants regarding intervention allocation.

### Data collection and management

We collect and store data using the Research Electronic Data Capture (REDCap) tool hosted by Aarhus University. REDCap is a secure, web-based application designed to support data capture for research [46]. The teachers will be asked to register the school class (class name, number of pupils, number of boys and girls), recruited for the project in RED-Cap. We inform the parents about the trial and the possibility to opt out of their child completing questionnaires in the trial via the school teachers. The teachers will register pupils with parental opt out in RED-Cap. The teachers will be asked to arrange time during school hours (in defined time-windows of two weeks) for the online completion of questionnaires and provide the pupils (including absentees) with the online access to the questionnaires. We e-mail two reminders to the teachers regarding the pupil questionnaires. A UNI-login is a unique identification number used in the Danish school system. It will be the key to link the three pupil questionnaires. The above procedure has been pilot tested and improved several times during the past years.

We will export data to a Stata file and data will be checked for double data entry and outliers.

### Statistical methods

Data will be analysed by a repeated measurement model with the systematic effect: region, type of school, school size, sex (pupil), class, time (three time points), intervention, interaction between time and intervention, and random effect of school, teacher/class within school and pupil within class.

Confidence intervals and standard errors will be found by bootstrapping to adjust for possible deviation from normality of the random effects.

We will perform four sensitivity analyses representing scenarios with data not missing at random. In these sensitivity analyses, missing outcomes will be substituted with predictions based on the analysis models above adding or subtracting 0.2*SD in the intervention or control arm.

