### Outcomes

The outcome measures are described in Table 1.

**Table 1 Tab1:** Description of outcome measures, assessed at baseline, 3 and 6 months among schoolchildren, the SELFCARE project

Measurement	Description
Demographic data	Data on age, sex, school, class, cohabitation and family socio-economic status will be collected as in the national Health Behaviour in School-aged Children survey
The Strengths and Difficulties Questionnaire (SDQ)-youth self-report [32]	The SDQ comprises 25 items describing psychological or behavioural attributes. The items have three response categories ‘‘very true’’, ‘‘somewhat true’’ or ‘‘not true’’. The instrument can generate five sub-scales scores (emotional problems, conduct problems, hyperactivity, peer problems, and prosocial behaviour). The total difficulties score is the sum of the subscale scores excluding the score of prosocial behaviour. The total difficulties score ranges from 0 to 40 with higher values indicating poorer behavioural and emotional functioning and well-being. The subscales ranges from 0 to 10 with higher scores indicating poorer functioning and well-being for four of the subscales (emotional, conduct, hyperactivity–inattention and peer problems) and better functioning and well-being for one of the subscales (prosocial). Goodmann et al. has shown a dose–response relationship between total difficulties scores and the risk of having or in a 3-year period developing a mental disorder [33]. The odds-ratio for having a mental disorder per one-point increase in the youth self-reported SDQ total difficulties score was 1.23 (95%CI 1.21 to 1.25). The odds-ratio for developing a mental disorder with-in a 3-year period per one-point increase in the youth self-reported SDQ total difficulties score was 1.16 (95% CI 1.13 to 1.18). These are results of a population-based observational study. However, Goodmann et al. argues that differences in mean total difficulties scores between intervention and control groups in experimental research can legitimately be interpreted as reflecting genuine differences in mental health [33]

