#### Primary outcome

We use self-reported changes from baseline in the SDQ total difficulties score [32] by the pupils as the primary outcome. SDQ measures behavioural and emotional functioning and social competencies, which is highly relevant according to WHO´s definition of mental health e.g. the ability to manage thoughts, emotions, as well as to build social relationships [1]. SDQ is recommended as a measure of child well- being in community settings such as schools [33].

Our primary end-point is 6 months after baseline. Our primary study population is the vulnerable sub group with a SDQ total difficulties score above the 80th percentile [34]. They will be taught the “.b” programme together with the whole class as a part of compulsory class room teaching.

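### Family socio-economic status and cohabitation are collected but not in the analysis model; adding them, each with time, is a cheap safeguard for pupils recruited after allocation

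*Protocol article*

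**What the plan says.** The Statistical methods section of the protocol article sets out a repeated measurement model. Its systematic effects are "region, type of school, school size, sex (pupil), class, time (three time points), intervention", followed by "interaction between time and intervention, and random effect of school, teacher/class within school and pupil within class". Sex and class are the only terms that describe the pupil. Class here presumably means grade, since the individual class is also a random effect.

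Table 1, under Outcomes, holds more on the pupil: "Data on age, sex, school, class, cohabitation and family socio-economic status will be collected". The table heading places its measures at baseline, 3 and 6 months.

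Under Recruitment, "it was not possible to include the pupils before the randomisation of the schools due to the logistics of teacher planning", and teachers were told that "it was an obligation for each teacher to recruit one 5–8 class with 15 to 28 pupils in a year from randomisation". Under Blinding: "It was not possible to blind either intervention providers or study participants regarding intervention allocation". The Randomisation section balances schools within region on type, size and number of teachers.

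The primary outcome is on the change scale ("We use self-reported changes from baseline in the SDQ total difficulties score"), and the primary population is the subgroup above the 80th percentile of that score. For missing outcomes, four sensitivity analyses shift model predictions up or down by 0.2 SD in one arm or the other.

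**The concern.** Randomising schools protects the mix of schools. It protects the mix of pupils less well when unblinded teachers choose classes up to a year later, and when parents learn of the trial, and may opt out, through those teachers. Family socio-economic status and cohabitation are the family-background measures that the trial holds, so they are the obvious values to use against an imbalance that arises after allocation.

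Three routes to bias in the time-by-intervention contrast stay open:

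1. Background predicts how SDQ changes over six months, and the arms differ in background.
2. Pupils of some backgrounds are lost more in one arm than in the other.
3. The subgroup is selected on a high baseline score. Pupils from the arm with the lower expected score then need a larger upward fluctuation to pass the cut-off, and they fall back further afterwards. A constant effect of background is enough for this.

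The planned sensitivity analyses do not close these routes. Their predictions come from the same model without family background, and the shift is the same for every pupil in an arm.

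**Working it through.** **The plan's own figures.** With two-sided alpha 0.05 (assumed; the article gives none), 80% power and equal groups, the t-test calculation gives 101.7 per group for 1.5 points (SD 3.8) and 970.1 for 0.7 points (SD 5.5). Rounded up, these are the stated 102 and 971. The point disputes neither; 1.5 and 0.7 serve only as yardsticks.

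**Assumed inputs.** The article gives no distribution of family background, no relation to SDQ and no loss rates. Every size below is therefore illustrative. Negative values favour the intervention. Clustering is ignored; it affects precision rather than the direction of these results.

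**Total population, simulated with no true effect** (2000 pupils, 1000 replicates, simulation error about 0.005 to 0.006). Background is a standardised score, 0.25 SD higher in the intervention arm, and lowers SDQ by 1.5 points per SD. Where loss is present, its log-odds are −1.8 − 0.8 × background; for loss in one arm only, the background term applies in the intervention arm alone. Entries are the bias in the 6-month contrast.

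| Effect of background on change | Loss related to background | Model as planned | Main effect added | Main effect and time interaction added |
|---|---|---|---|---|
| none | no loss | 0.01 | 0.01 | 0.01 |
| none | equal in both arms | 0.01 | 0.00 | 0.00 |
| none | one arm only | −0.05 | 0.00 | 0.00 |
| 0.3 points per SD | no loss | 0.07 | 0.07 | −0.01 |
| 0.3 points per SD | equal in both arms | 0.08 | 0.07 | 0.00 |
| 0.3 points per SD | one arm only | 0.06 | 0.10 | 0.00 |

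The fourth row checks by hand: 0.25 × 0.3 = 0.075. A main effect alone repairs only the one-arm-loss case with no effect on change. Where background alters change, the interaction is needed.

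**The same route with categories.** Bias = difference between arms in the share × difference in 6-month change between groups. With 10 percentage points and 1.0 SDQ point: 0.10 × 1.0 = 0.10, which is 0.10/0.7 = 14% of the planned effect. With 5 points and 0.5: 0.05 × 0.5 = 0.025. With 15 points and 1.5: 0.15 × 1.5 = 0.225.

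**Primary subgroup, constant effect of background, no loss.** Take a total SD of 5.5 and a change SD of 3.8, so the within-pupil error variance is 3.8²/2 = 7.22. If D is the difference between arms in expected baseline level, the expected fall-back in an arm is (7.22/5.5) × λ(z). Here z is the arm's standardised cut-off and λ the normal hazard. At the 80th percentile z = 0.84, λ = 1.40 and its slope is 1.40 × (1.40 − 0.84) = 0.78. The bias is then about −1.31 × 0.78 × D/5.5 = −0.19 × D.

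- Imbalance 0.1 SD, 0.5 points per SD: D = 0.05, bias −0.01.
- Imbalance 0.25 SD, 1.0 point per SD: D = 0.25, bias −0.05.
- Imbalance 0.5 SD, 1.5 points per SD: D = 0.75, bias −0.14.

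Direct simulation of the same settings gave −0.01 to −0.15. The top value is 0.15/1.5 = 10% of the planned effect. Adding background to the regression of change brought the second and third cases to within 0.01 of zero.

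**Against the planned standard errors** (no clustering): total population 5.5 × √(2/971) = 0.25, so 0.10 is 0.4 of a standard error; subgroup 3.8 × √(2/102) = 0.53, so 0.15 is 0.28 of one.

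**Gain in precision.** If the covariates explain 2 to 4% of residual variance, the standard error is multiplied by √0.98 = 0.99 to √0.96 = 0.98.

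**The case against.** The strongest reply is that the model already does most of the work. It holds the baseline measurement, a random pupil effect and the time-by-intervention term, so a stable difference in level drops out in the total population. A reader might infer from the covariate list that imbalance in family background and socially patterned loss go uncorrected altogether. The document does not support that: the first two rows of the table show a bias indistinguishable from zero, and the four 0.2 SD analyses do probe loss that is not at random. This part of the reply stands.

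Second, chance imbalance is not bias. Schools were randomised within region, and the random effects and bootstrap intervals are meant to cover chance differences between schools. With 54 and 56 schools and an assumed between-school SD of 15 percentage points, the chance standard error is 15 × √(1/54 + 1/56) = 2.86 points, or ±5.6 at 95%. A 10-point gap is 3.5 times that standard error and a 15-point gap 5.2 times, so either needs systematic selection. Teachers enrol whole classes, and the article describes no route that would sort them on family background. An untreated difference in change of 1.0 point would also exceed the whole planned effect of 0.7. For these reasons the 0.225 figure should not be relied on. At the chance limit, 0.056 × 1.0 gives 0.06.

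Third, completion in school hours, access for absentees and two reminders should limit loss. Adjusting for region, school factors, sex and grade is also a defensible primary model, and collecting a variable creates no duty to adjust for it. An analysis plan that is not shown may already name an adjusted analysis. All this is fair, and it makes the point a suggestion. It does not remove the subgroup route, which needs no loss and no effect of background on change, and which concerns the primary analysis.

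**Conclusion.** The point holds as a cheap improvement. Nothing in the stated model is wrong or contradictory. The facts that support the suggestion are plain in the article: the two variables are collected, they are not used, and pupils enter after allocation through unblinded teachers.

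The residual bias is of unknown and probably small size. Under the assumed inputs it is about 0.01 to 0.15 points against 1.5 in the primary subgroup, where the top value needs a 0.5 SD imbalance and 1.5 points per SD. In the total population it is up to about 0.1 against 0.7. These figures show what could happen; they do not estimate what will.

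**What to change.** Before outcomes are examined by arm, add baseline family socio-economic status and baseline cohabitation to the systematic effects, each with its interaction with time. Use baseline values only. Put the same terms into the predictions behind the four missing-data sensitivity analyses, and report the model without them alongside. Keep pupils with missing covariates in the analysis, by a missing category or by imputation, and state that adjustment is then partial.

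The cost is a line or two in the analysis plan and no new data. The downsides are a few extra parameters, imprecise self-report of family background in the younger pupils, and little gain in precision (about 1 to 2% of the standard error under the assumption above). Timing matters because covariates added after the results are seen would invite a charge of selection.

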**Methods:**

The pragmatic cluster two-armed randomised controlled trial includes 110 municipal or private schools from all five regions in Denmark; 191 school teachers and approximately 2000 pupils at 11–15 years of age. Exclusion criteria; for schools: < 100 pupils; for pupils: parental opt out. Our intervention consists of (A) a school teacher training programme and (B) the “.b”-programme delivered as part of compulsory class room teaching in schools to pupils at the age of 11–15 years. The pupils in the control schools receive education as usual. Our primary study population is the vulnerable subgroup with a Strengths and Difficulties Questionnaire (SDQ) total difficulties score > 80% percentile at baseline (approximately 400 pupils). The primary outcome is change in the SDQ total score by the pupils. We also evaluate the effectiveness among the total pupil study population and in girls and boys, respectively and use other measures on mental health. Data will be analysed with repeated measurement models taken clusters into account.

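### The listed random effects cancel from the change-from-baseline contrast, and the bootstrap protects it against correlated change only if whole schools are resampled, which the article does not state

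*Protocol article*

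**What the plan says.** Under Primary outcome the protocol article states: "We use self-reported changes from baseline in the SDQ total difficulties score". It then fixes the time point: "Our primary end-point is 6 months after baseline".

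Under Statistical methods the fixed part of the repeated-measures model includes "time (three time points), intervention, interaction between time and intervention", and the random part is "random effect of school, teacher/class within school and pupil within class". No random slope and no interaction of school or class with time is listed.

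The next sentence says how uncertainty is obtained: "Confidence intervals and standard errors will be found by bootstrapping to adjust for possible deviation from normality of the random effects". It does not say whether schools, classes, pupils or residuals are resampled.

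The abstract (Methods) gives the intent: "Data will be analysed with repeated measurement models taken clusters into account".

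**The concern.** Schools are randomised, and each teacher brings one class. Whatever happens to a class between baseline and 6 months (its teacher, class events, shared conditions when questionnaires are completed) can move its pupils in the same direction. The Discussion itself allows that teaching competence may influence effectiveness. Pupils' changes may then be correlated within class and school, and a valid standard error for the difference in change has to include that correlation.

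A random intercept covers pupils in a class having similar levels. It does not cover them having similar changes. If the bootstrap does not supply what the model leaves out, intervals for the contrast that answers the trial's question would be too narrow, and the abstract's assurance about clusters would not hold for that contrast.

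**Working it through.** **Inputs from the article.** Recruitment: 110 schools, 191 teachers with one class each, about 2000 pupils, about 400 of them in the vulnerable subgroup. Table 2: 54 and 56 schools, with 23/17/14 and 26/21/9 schools contributing 1/2/3 teachers. Sample size: "we expect a reduction of 1.5 score points (sd 3.8) in the SDQ total difficulties score among the vulnerable sub group", and "with a statistical power of 80%, it requires a study sample of 102 pupils in each group; 204 in total"; for the total population 0.7 points, SD 5.5, 971 per group.

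**Assumptions, not in the article.** Two-sided alpha 0.05. ICC of change, meaning the share of the variance of pupils' 6-month change that lies between classes or between schools, from 0.02 to 0.10.

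**1. The plan's own figures.** The t-based two-sample calculation at 80% power gives 101.7 and 970.06 per group, which round up to the stated 102 and 971. They reproduce as individually randomised calculations with no design effect, so no ICC can be recovered from them.

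**2. Algebra.** Write a score as y_t = fixed effects + u(school) + v(class) + w(pupil) + e_t. Then y_6 − y_0 = difference in fixed effects + e_6 − e_0. All three random effects drop out. With complete data the model variance of the 6-month interaction is 2σ_e²(1/n1 + 1/n0), which has no cluster component. With missing visits the cancellation is approximate.

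**3. Numerical check of the algebra.** The three-level intercept model was fitted to simulated data: 60 schools, 2 classes of 8 pupils each, 480 pupils per arm.
- School and class variances 0.1: fitted SE 0.27199, closed form 0.27199.
- School and class variances 20: 0.27555 and 0.27555.
- Class-by-time variance 1 added (residual variance 9): 0.28208 and 0.28208. The true SE in that setting is √[2·9·(2/480) + 2·1·(2/60)] = √(0.0750 + 0.0667) = 0.376.

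**4. Expected size.** Average cluster sizes are 400/191 = 2.1 and 2000/191 = 10.5 per class, and 400/110 = 3.6 and 2000/110 = 18.2 per school. The design effect is 1 + (m − 1)·ICC. For ICC 0.02 to 0.10 it is:
- subgroup: 1.022 to 1.109 (class), 1.053 to 1.264 (school);
- total population: 1.189 to 1.947 (class), 1.344 to 2.718 (school).

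Type I error is roughly 2[1 − Φ(1.96/√DE)]. For example, the total population at class level with ICC 0.05 has DE = 1.474 and error 0.106.

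**5. Simulation under the null.** 2000 runs per scenario with Table 2's structure, placing the correlated change at one level at a time. The table compares the test using the model SE with one using a bootstrap of whole schools within arm.

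| Population, level | Model SE, ICC 0 | 0.02 | 0.05 | 0.10 | School bootstrap, range over the four ICCs |
|---|---|---|---|---|---|
| Subgroup, class | 0.053 | 0.065 | 0.051 | 0.077 | 0.048–0.064 |
| Subgroup, school | 0.055 | 0.052 | 0.083 | 0.106 | 0.049–0.066 |
| Total, class | 0.048 | 0.071 | 0.114 | 0.168 | 0.049–0.060 |
| Total, school | 0.051 | 0.102 | 0.188 | 0.275 | 0.056–0.066 |

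The Monte Carlo SE near 5% is √(0.05·0.95/2000) ≈ 0.005, so differences of about 0.01 should not be read closely. The school-level figures for the total population exceed the formula (0.235 at ICC 0.10) because schools contribute between 1 and 3 classes. Table 2's counts give 99 + 95 = 194 classes against 191 stated; this does not affect the result.

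**The case against.** A reader might infer that the trial's primary test is invalid: that it treats pupils in a class as changing independently and that its error rate exceeds 5%. The article does not support that. Inference is by bootstrap, not by the model SE, and a bootstrap of whole schools restores near-nominal error with the model left exactly as written. The stated purpose of the bootstrap does not show that schools are resampled, but it does not rule it out, and the abstract states the intent to respect clustering. A journal article may also leave the resampling unit, and any cluster-by-time covariance, to an analysis plan that is not at hand. Nor does the article say in words that the random effects are intercepts only, although that is the natural reading.

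Three further points have force. An effect that is equal in every class creates no within-class correlation, so under a strict null the correlation must come from class events, teachers or shared conditions. In the primary population, with about 2 pupils per class, the inflation is small to moderate. The ICC range is an assumption throughout.

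These points make the conclusion conditional and limit its size. They do not remove it. The article sets out a specific random part that gives the key contrast no cluster variance, and it gives the bootstrap a purpose that addresses a different problem. Someone who followed the text literally with a parametric or residual bootstrap would carry out the stated plan and still miss the correlation.

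**Conclusion.** The concern holds in conditional form. The model as listed gives no protection against correlated change within class or school, and whether the bootstrap does depends on a unit that the article does not name. If whole schools are not resampled, and the ICC of change is 0.02 to 0.10, simulated type I error is about 5 to 11% for the primary vulnerable subgroup and about 7 to 28% for the secondary total-population analysis. The lower end for the subgroup cannot be told from nominal, so the main exposure is the total-population result. The cancellation is exact only with complete data and rests on reading the random effects as intercepts. That class appears in both the systematic and the random part is a separate wording matter, and this conclusion does not depend on it.

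**What to change.** Make at least one of two changes, preferably both:

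- add school-by-time and class-by-time random effects to the model;
- state that the bootstrap resamples whole schools, within region and arm, keeping all classes, pupils and visits of a drawn school together.

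With about 2 subgroup pupils per class, a class-by-time variance may not be estimable; the school bootstrap then suffices by itself. The simulation resampled within arm only, and the smallest region has 10 schools, so the behaviour of the region-stratified version should be checked before it is fixed.

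No design or data change is needed. The cost is wider intervals, by a factor of about √DE. For ICC 0.02 to 0.10 that is 1.01 to 1.12 in the subgroup (√1.022 to √1.264) and 1.09 to 1.65 in the total population (√1.189 to √2.718). For the stated subgroup effect with about 200 pupils per group, power with a valid test stays at 0.94 to 0.97 over that range.
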